### 2.8. Outcome measures

Outcome measures are listed in Table 2.

**Table 2 T2:** Detailed descriptions of the endpoints.

Endpoints	Explanation
Duration of Gr4 CIN (cycle 1)	Duration (in d) of absolute neutrophil count (ANC) < 500/μL in the first chemotherapy cycle
Incidence of Gr 3–4 CIN (cycle 1)	Subjects with ANC < 1000/μL in the first chemotherapy cycle
Severity of CIN (cycle 1)	Minimum ANC level in the first chemotherapy cycle
Time to ANC recovery (cycle 1)	Time (in d) from day 1 of chemotherapy to ANC > 1000/μL after the nadir in the first chemotherapy cycle
Febrile neutropenia (FN) incidence (cycle 1–4)	Development of FN until 28 d after the end of cycle 4. FN is defined as an oral temperature rise to 38.3°C or higher or a fever of 38.0°C or higher that lasts for 1 h or more with an ANC <500/mm^3^ or with an ANC <1000/mm^3^ that is expected to decrease to <500/mm^3^ within 48 h
Incidence of CIN-related dose delay (cycle 1–4)	Delay of chemotherapy schedule due to development of CIN
Relative dose intensity (RDI) (cycle 1–4)	Dividing the total dose of chemotherapy (mg/m^2^) by the total administration period, and the value was expressed as a percentage based on the full dose intensity (Table 1)
Pegteograstim-related AEs (cycle 1–4)	Occurrence of bone pain and pneumonitis during cycles 1–4

AEs = adverse events, CIN = chemotherapy induced neutropenia, Gr = grade.

-Duration of Gr4 CIN (cycle 1): duration (in days) of ANC < 500/μL in the first chemotherapy cycle.-Incidence of Gr 3 to 4 CIN (cycle 1): subjects with ANC < 1000/μL in the first chemotherapy cycle.-Severity of CIN (cycle 1): minimum ANC level in the first chemotherapy cycle.-Time to ANC recovery (cycle 1): time (in days) from day 1 of chemotherapy to ANC > 1000/μL after the nadir in the first chemotherapy cycle.-FN incidence (cycle 1–4): development of FN until 28 days after the end of cycle 4. FN is defined as an oral temperature rise to 38.3°C or higher or a fever of 38.0°C or higher that lasts for 1 hour or more with an ANC <500/mm^3^ or with an ANC <1000/mm^3^ that is expected to decrease to <500/mm^3^ within 48 hours.-Incidence of CIN-related dose delay (cycle 1–4).-Relative dose intensity (RDI) (cycle 1–4): RDI is calculated by dividing the total dose of chemotherapy (mg/m^2^) by the total administration period, and the value was expressed as a percentage based on the full dose intensity (Table 1).-Pegteograstim-related AEs (cycle 1–4): the occurrence of bone pain and pneumonitis during cycles 1 to 4.

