### 2.9. Criteria for discontinuation of study drug and study drop-out

Criteria for discontinuation of the study drug are: Completion of the planned 4 cycles; Disease progression according to RECIST v1.1, or unacceptable AEs requiring discontinuation of chemotherapy; Withdrawal of consent, and pregnancy.

The drop-out criteria are; withdrawal of consent and; pregnancy.

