### 2.11. Statistical analysis

The primary analysis is performed in the per-protocol (PP) set, considering the non-inferiority design. The per-protocol group is defined as patients who do not have any of these following significant deviations from the clinical trial protocol: Failure to administer the study drug (pegteograstim) within the scheduled period (same-day arm: within 4 hours, Next-day arm: 24–36 hours); Discontinuation of CBCs before < 50% of tests (on 3 or fewer days) or until ANC reaches > 500/μL, and; development of FN and treatment with additional filgrastim at the discretion of the investigator.

Demographics, clinical presentation, perioperative clinical findings, and laboratory values are summarized using descriptive statistics. Continuous variables are described by median values, and categorical variables are described by absolute numbers and percentages. *T* test is used for group comparison of continuous variables such as duration of Gr4 CIN, severity of CIN, and RDI. Chi-square test or Fisher exact test is used for group comparison of categorical variable values such as incidence of Gr 3 to 4 CIN (Cycle 1), FN, CIN-related dose delay, and pegteograstim-related AEs. Time to ANC recovery is analyzed by the method of Kaplan–Meier.

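### The cycle 1–4 dose-intensity and CIN-delay endpoints do not register chemotherapy cycles that are never given, so they can mask a difference in delivery between arms

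*Protocol article*

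**What the plan says.** Two secondary endpoints describe chemotherapy delivery over cycles 1–4. For RDI, section 2.8 states: "RDI is calculated by dividing the total dose of chemotherapy (mg/m^2^) by the total administration period, and the value was expressed as a percentage", and the reference is the full dose intensity in Table 1. Table 2 gives the same formula. Table 1 lists doses per 2-week or 3-week cycle, so the reference is a rate and not a four-cycle total. The administration period is not defined further.

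The delay endpoint is explained in Table 2 as "Delay of chemotherapy schedule due to development of CIN". A cycle omitted for good, or a permanent stop, is not mentioned.

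Section 2.9 lists among the reasons for ending study drug "Completion of the planned 4 cycles", disease progression and "unacceptable AEs requiring discontinuation of chemotherapy". The next sentence is narrower: "The drop-out criteria are; withdrawal of consent and; pregnancy". A patient who stops for toxicity or progression is therefore not a drop-out.

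Section 2.11 compares RDI between arms by t test. For delay, "Chi-square test or Fisher exact test is used for group comparison of categorical variable values".

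**The concern.** RDI and CIN-related delay are where the trial would show whether the timing of the injection affects how much chemotherapy patients receive. Section 3 gives the reason to look: injection within 24 hours of chemotherapy may worsen neutropenia. One possible result of worse neutropenia is that chemotherapy ends early.

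That result is the one these definitions handle poorly. When treatment stops, dose and time stop accumulating together, so the ratio does not fall. When CIN ends treatment, no later cycle exists that could be late, so no delay event arises. A patient who lost half the planned chemotherapy can then look better on both endpoints than one who received all of it a week late. If such stops were more common in one arm, the comparison could show little or no difference in delivery where one exists.

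**Working it through.** **The plan's own figure.** None is stated for RDI or delay. The only sample-size figure is for the primary endpoint (section 2.10: margin 0.6 days, SD 1.4 days, 5% level, 80% power). It reproduces with a one-sided 5% level: 2 × (1.645 + 0.842)² × 1.4² / 0.6² ≈ 67.3, so 68 per group and 136 in total; 136 / 0.85 = 160. Nothing below changes it.

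**Inputs.** Four planned cycles (section 2.9); cycle length L = 14 or 21 days (Table 1, section 2.6); full dose at the start (section 2.3). The 7-day delay and the 20% reduction are illustrative assumptions.

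**Formula.** Let dᵢ be the fraction of the Table 1 dose given in cycle i, and T the administration period in days. Then RDI = (Σdᵢ / T) / (1 / L) = L × Σdᵢ / T. Two readings of T are compared: actual time on treatment, counted to the end of the last cycle's interval, and a fixed planned period of 4L (56 or 84 days).

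| Course | Actual T, L = 14 | Actual T, L = 21 | Fixed T = 4L |
|---|---|---|---|
| Stop after 1, 2 or 3 full, on-time cycles | 100% | 100% | 25%, 50%, 75% |
| Four full cycles, one 7-day delay | 56/63 = 88.9% | 84/91 = 92.3% | 100% |
| Four on-time cycles, 20% cut in cycles 2–4 | 3.4/4 = 85% | 85% | 85% |
| Stop after cycle 2, given 7 days late | 28/35 = 80.0% | 42/49 = 85.7% | 50% |
| Stop after cycle 2, cut by 20% | 1.8/2 = 90% | 90% | 45% |
| Stop after cycle 2, late and cut | 14 × 1.8/35 = 72.0% | 21 × 1.8/49 = 77.1% | 45% |

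On the actual-time reading, the patient in the first row scores 100 − 88.9 = 11.1 points (2-week) or 100 − 92.3 = 7.7 points (3-week) above the completer with one delay. On the fixed-period reading the early stop is visible, but the delayed completer scores 100%, so RDI no longer registers delay.

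**Delay endpoint.** Under the Table 2 wording, a CIN-caused stop with no previous CIN delay gives no event. A stop preceded by a CIN delay is already an event. A stop for another toxicity is not a CIN delay and should not be one.

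**Arm level, illustration only.** The documents give no rate of early stopping. Assume 5% in the next-day arm and 5% to 20% in the same-day arm, all stops after cycle k, and every delivered cycle full and on time in both arms. The difference in mean percentage of planned dose is (p_same − p_next) × (1 − k/4) × 100. It runs from 0 (equal rates) to (0.20 − 0.05) × 0.75 × 100 = 11.25 points (20% against 5%, k = 1). The difference in RDI over actual time is 0 throughout.

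**The case against.** The strongest reply is that no sentence gives an early stopper 100% or no delay. The administration period is undefined, the endpoint is labelled for cycles 1–4, and a planned-period denominator gives 25%, 50% or 75%. That stands as a limit on the wording, but it does not rescue the definition: a fixed planned period makes RDI blind to delay. Taking the longer of actual and planned time would register both, but nothing in the text suggests it.

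A second reply is that such detail belongs in the full protocol or SAP, which is not shown. Rules for early stops may well be there. The formula itself, however, is stated in the article twice, and the point is about what that formula does.

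A reader might go further and infer that the plan scores every toxicity stop as the best outcome, or that it favours the worse arm. The documents do not support this:

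- 100% and no delay arise only if no reduction or delay came before the stop.
- The analysis set for these endpoints is not stated. Section 2.11 makes per-protocol the primary analysis and lists febrile neutropenia treated with additional filgrastim as a deviation, so some CIN-caused stops might be excluded altogether.
- Severe cycle 1 neutropenia is captured by the primary endpoint, grade 3–4 incidence and nadir. Febrile neutropenia is followed until 28 days after cycle 4.
- No stop rates are given, and the illustration shows masking, not reversal.

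**Conclusion.** The point holds in a limited form. As worded, RDI over cycles 1–4 does not register cycles never given, and the delay endpoint has no event for a permanent stop caused by CIN. A patient who stops after full-dose, on-time cycles can score 100% and no delay, above a completer with one 7-day delay at 88.9% or 92.3%. The two endpoints can therefore mask a difference between arms in chemotherapy delivery.

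This rests on reading the administration period as actual time on treatment, the natural sense of the words. It also rests on such patients being included in the secondary analyses, which section 2.9 suggests but no text settles. The effect on the arm comparison cannot be sized from the documents. The primary endpoint and the sample size are unaffected. The change is worth making because it is cheap and these endpoints are the trial's measures of chemotherapy delivery.

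**What to change.** In section 2.8 and Table 2:

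1. Redefine the delay endpoint as *CIN-related delay or CIN-related permanent discontinuation of chemotherapy in cycles 1–4*.
2. Define the administration period for RDI as actual time on treatment, and keep that RDI.
3. Alongside it, report by arm for all patients the dose delivered as a percentage of the planned four-cycle dose, with undelivered cycles as zero, and the number of cycles completed. Tabulate the reasons for stopping.

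The delivered-dose measure should follow one rule whatever the reason for stopping. A denominator that changed between toxicity and progression would depend on the investigator's attribution in an open-label trial.

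**Cost.** Wording of two secondary endpoint definitions and one added descriptive table. Section 2.7 already has dose and adverse events assessed in cycles 2–4. Section 2.12 mentions reasons only for withdrawal from the study, so a case report form field for the reason chemotherapy stopped may be needed. The delivered-dose figure will look lower than RDI, will also reflect stops unrelated to injection timing, such as progression, and is less comparable with reports that use delivered cycles only. Keeping RDI beside it limits that loss.

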### 2.9. Criteria for discontinuation of study drug and study drop-out

Criteria for discontinuation of the study drug are: Completion of the planned 4 cycles; Disease progression according to RECIST v1.1, or unacceptable AEs requiring discontinuation of chemotherapy; Withdrawal of consent, and pregnancy.

The drop-out criteria are; withdrawal of consent and; pregnancy.

### 2.10. Sample size calculation

The primary endpoint of the study is duration of Gr4 CIN. In prior studies using the next-day administration method, the duration of Gr4 CIN was approximately 2 to 2.5 days. Considering the non-inferiority margin of 0.6 days and equivalence margins of 1 to 2.1 days in previous studies,^[2,3]^ 0.6 days of Gr4 CIN duration was selected for the non-inferiority margin. In order to verify the non-inferiority of 0.6 days (standard deviation 1.4 days), a significance level of 5% and power of 80% were estimated. This resulted in the need for 136 patients, 68 per group. Adjusting for sample size by expecting a drop-out rate of 15% in each treatment group, we planned for enrollment of 160 total subjects, 80 subjects in each treatment group. The study subject registration period was assumed to be 2 years, and the follow-up period was assumed to be 3 months.

### 2.11. Statistical analysis

The primary analysis is performed in the per-protocol (PP) set, considering the non-inferiority design. The per-protocol group is defined as patients who do not have any of these following significant deviations from the clinical trial protocol: Failure to administer the study drug (pegteograstim) within the scheduled period (same-day arm: within 4 hours, Next-day arm: 24–36 hours); Discontinuation of CBCs before < 50% of tests (on 3 or fewer days) or until ANC reaches > 500/μL, and; development of FN and treatment with additional filgrastim at the discretion of the investigator.

Demographics, clinical presentation, perioperative clinical findings, and laboratory values are summarized using descriptive statistics. Continuous variables are described by median values, and categorical variables are described by absolute numbers and percentages. *T* test is used for group comparison of continuous variables such as duration of Gr4 CIN, severity of CIN, and RDI. Chi-square test or Fisher exact test is used for group comparison of categorical variable values such as incidence of Gr 3 to 4 CIN (Cycle 1), FN, CIN-related dose delay, and pegteograstim-related AEs. Time to ANC recovery is analyzed by the method of Kaplan–Meier.

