## 1. Introduction

### 1.1. Background

Chemotherapy-induced neutropenia (CIN) is one of representative adverse events (AEs) of cytotoxic chemotherapy that^[1]^ increases risk of febrile neutropenia (FN) and related mortality,^[2]^ reduces the effects of chemotherapy due to dose-limiting toxicity, and^[3]^ increases costs related to treatment of FN.^[4]^ Since CIN occurs most frequently during the first cycle of chemotherapy and adversely affects the clinical outcome, primary prophylaxis using granulocyte-colony-stimulating factor (GCSF) is recommended at the beginning of chemotherapy cycle 1 in patients with high-risk or moderate risk with risk factors.^[1]^

Pegylated granulocyte-colony-stimulating factor (peg-GCSF) was developed to increase the half-life to 46 to 72 hours by attaching polyethylene glycol to filgrastim so that only 1 administration per cycle is necessary to prevent CIN. A single injection of peg-GCSF showed an equivalent effect to daily filgrastim therapy in a comparative study.^[5]^ Based on the mechanism of action of peg-GCSF and results of prior prospective and meta-analysis studies,^[3,6]^ administration of peg-GCSF 24 to 72 hours after completion of chemotherapy is recommended.^[1]^ Patients in which the next-day method (administration after 24 hours post-chemotherapy) was implemented had fewer days in Grade (Gr) 4 neutropenia than the same-day method (administration within 4 hours post-chemotherapy). CIN was also less severe in the next-day group.

However, approximately 13% of patients receive same-day peg-GCSF probably due to the inconvenience of providing an additional hospitalization or hospital visit for administration of the peg-GCSF.^[7]^ In addition, in some retrospective studies or subgroup analyses, the same-day method was comparable or superior to the next-day method in preventing CIN in multi-day (3 to 5 days) regimens in which myelosuppressive agent administration was concentrated on day 1.^[3,8]^ Therefore, there is a need to reevaluate the efficacy of the same-day method in such cases.

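### The non-inferiority test rests on a per-protocol set that excludes patients for post-randomization events, including febrile neutropenia treated with discretionary filgrastim, and the 15% drop-out allowance does not say whether it covers these losses

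*Protocol article*

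**What the plan says.** Section 2.11 of the protocol article fixes the analysis set for the non-inferiority comparison: "The primary analysis is performed in the per-protocol (PP) set, considering the non-inferiority design". It names no other set. Three kinds of deviation remove a patient:

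- an injection outside the scheduled window, "same-day arm: within 4 hours, Next-day arm: 24–36 hours";
- an incomplete count series, "Discontinuation of CBCs before < 50% of tests (on 3 or fewer days) or until ANC reaches > 500/μL";
- "development of FN and treatment with additional filgrastim at the discretion of the investigator".

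Section 2.6 says that the trial is open-label. Section 2.8 lists FN as a secondary endpoint: "Development of FN until 28 d after the end of cycle 4".

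Section 2.10 obtains 68 per arm and raises this to 80: "Adjusting for sample size by expecting a drop-out rate of 15% in each treatment group". Section 2.9 defines drop-out narrowly: "The drop-out criteria are; withdrawal of consent and; pregnancy". None of the three per-protocol exclusions appears in that definition.

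**The concern.** All three exclusions are decided after randomization, but they differ in how closely they are tied to the outcome.

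- **FN with filgrastim.** This is the most serious. FN is a consequence of deep or prolonged neutropenia, so the patients removed are likely to be those with long Grade 4 duration, which is the primary endpoint. The decision to add filgrastim is left to an investigator who knows the arm. If same-day dosing is truly worse, more such patients would leave that arm and the observed difference would shrink.
- **Incomplete counts.** This is linked to the neutrophil course. Section 2.7 allows counts to stop once the ANC has risen on two consecutive days and exceeds 1000. A fast recoverer tested only on days 5, 6 and 7 would comply with that rule, yet on a literal reading could be excluded for having three test days. At the other extreme, a patient whose counts stop while the ANC is still low is also excluded.
- **Dosing window.** The windows differ by arm. Section 1.1 names the "inconvenience of providing an additional hospitalization or hospital visit for administration of the peg-GCSF" as a probable obstacle to next-day dosing. Timing is settled before the day 5 to 9 counts, so this exclusion does not depend on the outcome, but it may thin the next-day arm.

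At stake is whether a non-inferiority conclusion reflects the randomized comparison or the way the set was formed. A secondary matter is power: the stated 80% needs 68 analysable patients per arm, and 80 × 0.85 = 68 leaves no reserve.

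**Working it through.** **Inputs from Section 2.10:** margin 0.6 days, SD 1.4 days, significance level 5%, power 80%, 68 per arm before and 80 per arm after a 15% allowance, next-day Grade 4 duration about 2 to 2.5 days. **Assumed:** true difference 0 for the sample size, and a one-sided 5% level. The article does not state sidedness, but only this reproduces its figure; one-sided 2.5% gives 86 per arm.

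**1. The plan's own figure.** n = 2 × (1.645 + 0.842)² × 1.4² / 0.6² = 67.3, rounded up to 68 per arm (136 in total). 68 / 0.85 = 80 per arm (160 in total). Both reproduce.

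**2. Power by total loss from the per-protocol set.** Power = Φ(0.6 / (1.4 × √(2/n)) − 1.645).

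| Total loss from 80 per arm | n per arm | Power |
|---|---|---|
| 0% | 80 | 86% |
| 15% | 68 | 80% |
| 20% | 64 | 78% |
| 25% | 60 | 76% |
| 30% | 56 | 73% |

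The documents give no exclusion rates, so the loss column is a range of assumptions.

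**3. Effect of an outcome-dependent exclusion.** Everything here beyond the margin, SD and next-day mean is assumed. Set the true difference at the margin, so the next-day mean is μ = 2.0 or 2.5 and the same-day mean is μ + 0.6. Let excluded FN/filgrastim patients average m = 4 or 5 days in either arm, with excluded fractions f_s (same-day) and f_n (next-day).

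- Retained means: (μ + 0.6 − f_s·m)/(1 − f_s) and (μ − f_n·m)/(1 − f_n). Their difference is D.
- Standard error: 1.4 × √(1/(80(1 − f_s)) + 1/(80(1 − f_n))).
- False non-inferiority rate: Φ((0.6 − D)/SE − 1.645).

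Example with μ = 2.0, m = 5, f_s = 10%, f_n = 5%: the retained means are 2.333 and 1.842, D = 0.491 and SE = 0.230, so the rate is Φ(0.109/0.230 − 1.645) = 12%.

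| Excluded, same-day vs next-day | D (days) | False non-inferiority (nominal 5%) |
|---|---|---|
| 10% vs 10% | 0.67 | 2.7% |
| 10% vs 5% | 0.49 to 0.58 | 6 to 12% |
| 15% vs 5% | 0.33 to 0.52 | 10 to 31% |

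The inflation comes from unequal exclusion. Equal exclusion works against non-inferiority in this model.

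**4. Power if two sets must agree.** Take 68 of 80 per arm in the per-protocol set, all 80 with data, and a true difference of 0 in both sets. The two test statistics have correlation √(68/80) = 0.922. The limits are 0.6/0.2214 − 1.645 = 1.066 for 80 per arm and 0.6/0.2401 − 1.645 = 0.854 for 68 per arm. The bivariate normal probability below both is 0.785, or about 78%, against 80% for the per-protocol set alone.

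**The case against.** A per-protocol analysis has a proper place here. The aim in Section 1.2 concerns the effect of injection timing, and an all-randomized analysis can itself drift toward non-inferiority when patients receive the other arm's schedule. This stands, and it is the reason to require both sets rather than replace one with the other. It does not justify removing patients for an event that follows from the outcome.

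Four stronger readings are tempting, and the documents do not support them.

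- **That exclusions exceed 15% and power is below 80%.** No exclusion rate is given. Section 2.10 does not say that its drop-out rate means only the Section 2.9 criteria, so it may be intended as a general allowance. If all losses together stay at or below 15%, power is as stated. At 20% the cost is about 2 percentage points.
- **That exclusions will be unequal, in a known direction.** This is a forecast. Section 1.1 offers inconvenience as a probable reason for same-day use in practice, not as a rate of missed windows in a trial. Mistimed injections may thin the next-day arm while FN exclusions thin the same-day arm.
- **That the dosing-window rule is the main source of bias.** It is settled before the outcome is measured. The FN/filgrastim and count-series rules are the weaker points.
- **That no all-randomized analysis will be done.** The article condenses a fuller protocol, and a supportive analysis may be specified elsewhere. What the article does fix is that the primary conclusion is drawn from the per-protocol set.

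**Conclusion.** The point holds in this form: the primary non-inferiority conclusion is drawn from a set defined partly by post-randomization events, and one of those events is closely tied to the primary endpoint and partly at open-label discretion. If same-day dosing is worse, that exclusion can favour non-inferiority. Its size depends on unknown rates. Under the assumptions shown, the false non-inferiority rate runs from 2.7% with equal exclusion to about 31% with 15% against 5%. These figures illustrate sensitivity and do not predict the trial's error rate, and the net direction across all three exclusions is not documented.

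The 15% allowance needs clarification and is not an arithmetic error. The per-protocol exclusions fall outside the stated drop-out definition in kind; whether they exceed the allowance in number cannot be known from the article.

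**What to change.** **Section 2.11.** Declare non-inferiority only if the upper confidence limit for the difference (same-day minus next-day) is below 0.6 days in both:

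- (a) all randomized patients who started cycle 1, analysed as randomized, with FN/filgrastim patients kept in, and with pre-specified analysis rules for their Grade 4 duration and for incomplete count series;
- (b) a per-protocol set that does not exclude on FN or filgrastim.

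Report per-protocol exclusions by arm and reason.

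**Section 2.10.** State that the 15% is the total expected loss from the per-protocol set, or give power as the range in the working (80%, 78%, 76% and 73% at 15%, 20%, 25% and 30% total loss).

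**Cost.** The success rule and the sample size text both change, so this is a protocol change as well as an analysis-plan change. Requiring agreement lowers power from 80% to about 78% if 68 of 80 per arm are in the per-protocol set and all 80 have data. Section 2.12 already commits to seeking endpoint data after withdrawal, which set (a) needs. If enrolment were raised instead to keep 68 per arm in the per-protocol set, a 20% total loss would need 68/0.80 = 85 per arm and a 25% loss 68/0.75, rounded up to 91.

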### 2.7. Evaluation and outcome measure

During cycle 1, a complete blood count (CBC) test is performed every day from day 5 to 9. If the ANC rises for 2 consecutive days before day 9 and is over 1000/mm^3^, CBCs can be stopped. Conversely, if the ANC does not recover to 1000/mm^3^ or more until day 9, the daily CBC should be continued until the ANC recovers to 1000/mm^3^. From cycle 2 to 4, anticancer treatment is performed according to general practice; and neutropenic fever, dose of chemotherapy, and AEs are assessed.

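### The per-protocol CBC criterion contradicts itself and can conflict with the section 2.7 stopping rule, so some compliant early recoverers may be excluded from the primary analysis, depending on the reading

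*Protocol article*

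**What the plan says.** Section 2.7 of the protocol article fixes the blood-count schedule: "During cycle 1, a complete blood count (CBC) test is performed every day from day 5 to 9". That is five tests. The same section allows an early stop: "If the ANC rises for 2 consecutive days before day 9 and is over 1000/mm^3^, CBCs can be stopped". For patients who have not recovered by day 9, "the daily CBC should be continued until the ANC recovers to 1000/mm^3".

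Section 2.11 chooses the analysis set: "The primary analysis is performed in the per-protocol (PP) set, considering the non-inferiority design". One of the deviations that removes a patient from that set begins with a test count, "Discontinuation of CBCs before < 50% of tests (on 3 or fewer days"); with its ANC limb the whole clause is "Discontinuation of CBCs before < 50% of tests (on 3 or fewer days) or until ANC reaches > 500/μL". No exemption is given for a stop that section 2.7 allows.

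Table 2 in section 2.8 defines the primary endpoint as "Duration (in d) of absolute neutrophil count (ANC) < 500/μL in the first chemotherapy cycle".

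**The concern.** The parenthesis in section 2.11 should explain the percentage, but on a five-test schedule the two define different sets of patients. They differ at three tests, which is the count a patient has after stopping on day 7 under section 2.7. A patient can therefore follow the monitoring rule exactly and still meet one version of the deviation.

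This matters for three reasons. The clause decides who is in the primary comparison. The patients in dispute are identified by their ANC course after randomization, from which the primary endpoint is derived, so excluding them would be selection on the outcome. And the trial is open-label (section 2.6), so a reading left open could be settled after ANC results by arm are known.

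**Working it through.** **Inputs.** Five scheduled tests and the stopping rule come from section 2.7; the deviation clause from section 2.11; the margin of 0.6 days, SD of 1.4 days, 5% significance level, 80% power and 15% drop-out from section 2.10.

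**The plan's own sample size.** With a true difference of 0 and a one-sided 5% level (both assumed; neither is stated), n per group = 2 × (1.645 + 0.842)² × 1.4² / 0.6² ≈ 67.3, rounded up to 68. Then 68 / 0.85 = 80 per group, 160 in total. The stated figures reproduce, and the wording problem does not affect them.

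**The two limits on a five-test schedule.**

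| Tests done | Share of 5 | Under 50%? | Three or fewer days? |
|---|---|---|---|
| 2 | 40% | yes | yes |
| 3 | 60% | no | yes |
| 4 | 80% | no | no |
| 5 | 100% | no | no |

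They disagree only at three tests.

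**Tests at a permitted stop.** Taking day 5 as the first scheduled value, two consecutive rises need day 5 < day 6 < day 7. With the day-7 ANC over 1000, the patient may stop on day 7 after three tests. A stop on day 8 means four tests, which neither limit catches.

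**Primary outcome of a day-7 stopper.** The day-7 value is over 1000, so only days 5 and 6 can be below 500. The observed Grade 4 duration is 0, 1 or 2 days.

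**Is the day-7 stopper excluded?**
- If the day count governs and each side of the word *or* is a deviation by itself: excluded.
- If the percentage governs: kept, because 60% is not under 50%.
- If the deviation is stopping before either target (half the tests, or ANC above 500) has been reached: kept, because ANC is already over 1000.

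**Size of a possible bias (illustration only).** Let p_N and p_S be the shares removed from the next-day and same-day arms. Assume mean durations of 2.0 (next-day) and 2.2 (same-day) among those kept, and 0 Grade 4 days among those removed. The difference is same-day minus next-day, so smaller values favour non-inferiority.

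- All patients: 2.2 × (1 − p_S) − 2.0 × (1 − p_N)
- After exclusion: 2.2 − 2.0 = 0.20

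| p_N | p_S | All patients | After exclusion | Movement |
|---|---|---|---|---|
| 30% | 15% | 1.87 − 1.40 = 0.47 | 0.20 | 0.27 toward non-inferiority |
| 20% | 15% | 1.87 − 1.60 = 0.27 | 0.20 | 0.07 toward |
| 20% | 20% | 1.76 − 1.60 = 0.16 | 0.20 | 0.04 away |
| 15% | 30% | 1.54 − 1.70 = −0.16 | 0.20 | 0.36 away |

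Against the 0.6-day margin, 0.27 is 45% and 0.36 is 60%. Zero days among those removed is the extreme case. With 1 day in both arms, the first row moves by 0.30 × (2.0 − 1) − 0.15 × (2.2 − 1) = 0.12 days instead of 0.27.

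**The case against.** The best defence is that section 2.11 lists significant deviations from the protocol, and a stop that the protocol allows is not naturally a deviation. Two of the three readings above keep the patient. Early stopping is optional, only stops at three tests are clearly in dispute, and the article condenses a full protocol that is not shown. This stands as far as the consequence goes: the text does not establish that compliant patients are excluded. It does not remove the defect, because the criterion is printed with two incompatible limits and no exemption.

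The percentage might refer to a longer series for patients tested past day 9: three of six tests is 50%, three of seven is 43%. That does not help a patient who stops on day 7 of a five-test schedule.

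The different thresholds (500 in section 2.11, 1000 in section 2.7) may be deliberate, since the primary endpoint uses 500. The text does not say so.

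A reader might infer two stronger conclusions, and the documents support neither.

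- **That the rule favours non-inferiority.** This would follow if next-day patients recover faster, as some studies cited in the Discussion found. But the article also cites data favouring same-day dosing in multi-day regimens, and the last two rows of the table move the other way.
- **That power falls to about 70%.** Removing 25% of patients leaves 51 of 68 per arm, and with SD 1.4 the power would be Φ(0.6 / (1.4 × √(2/51)) − 1.645) ≈ 70%. But taking out a block of zeros also reduces the SD. If all patients have SD 1.4 and those kept average 2.0 days, the remaining variance is (1.96 − 0.25 × 0.75 × 2.0²) / 0.75 = 1.61, so SD is 1.27 and power about 77%. If instead the overall mean is 2.0, those kept average 2.67, the remaining SD is 0.91 and power about 95%. The same formula thus gives anything from 70% to 95%, so no loss can be claimed.

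**Conclusion.** The point holds in a limited form. Section 2.11 is wrong as written: its percentage and its day count cannot both apply to five tests, and the day count can catch a patient who stopped on day 7 as section 2.7 permits. Whether that patient leaves the primary analysis depends on the reading, and the text does not choose one. If exclusion applies, it selects on the primary outcome.

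The shares removed, the means of 2.0 and 2.2 days and the zero durations in the bias table are all assumptions, so the table shows sensitivity and is not an estimate. The conclusion about the wording rests only on the schedule and the two limits, not on the table. Because the clause defines the primary population, it should be settled before analysis.

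**What to change.** Amend the per-protocol definition in section 2.11 before analysis:

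1. Give one test-count limit that agrees with its percentage: fewer than 3 of the 5 scheduled tests (under 50%).
2. State that stopping CBCs as section 2.7 permits is not a deviation and that these patients stay in the per-protocol set. The exemption is needed as well as the corrected count: if the two-day rise were taken as met by day 6, after two tests (40%), the corrected limit alone would still exclude the patient.
3. State whether the test-count limb and the ANC limb are separate deviations or must both be present.
4. Reconcile the ANC threshold in section 2.11 (500/μL) with that in section 2.7 (1000/mm³), or explain why they differ.

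Do not add a silent rule that untested days count as 0 Grade 4 days. No passage supports it, and the section 2.7 stopping rule does not require a nadir to have been seen before the rise. If such a rule is needed, state it as an assumption and check it in a sensitivity analysis.

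The cost is a short rewording. No patients or tests are added, and patients who might have been removed are kept.
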